# Reducing stigma and increasing workplace productivity due to mental health difficulties in a large government organization in the UK: a protocol for a randomised control treatment trial (RCT) of a low intensity psychological intervention and stigma reduction programme for common mental disorder (Prevail)

**DOI:** 10.1186/s12889-020-09054-0

**Published:** 2020-06-09

**Keywords:** Randomised control trial, Prevail, Work-based intervention, Self-stigma, Stigma, Avoidant coping, Absenteeism, Presenteeism

## Abstract

**Background:**

Common mental disorders are the leading cause of workplace absences. While the reasons for this are multifarious, there is little doubt that stigma related to common mental disorder plays a large role in sickness absence and in poor help-seeking. Frequently both managers and staff are unsure of how to approach and intervene with mental health related problems. We have therefore devised a mental health intervention programme (Prevail) that aims to reduce stigma and to educate staff about evidence-based low intensity psychological interventions. These can be used by the individual, as well as in collaboration with managers via co-production of problem-focussed solutions, with the aim of improving mental health, reducing sickness absence, and increasing workplace productivity.

**Methods:**

This two-armed cluster randomised control trial (RCT) will evaluate the effectiveness of Prevail. Eighty managers at a large UK government institution (the DVLA) and their teams (approximately 960 employees) will be randomised into the active intervention group or control (employment as usual) arms of the study. All participants will be invited to complete a series of questionnaires related to mental health stigma, their current and past mental health, and their recent workplace productivity (absenteeism and presenteeism). All employees in the active arm will receive the Prevail Staff intervention, which covers stigma reduction and includes psychoeducation about evidence-based low intensity psychological interventions for common mental disorder. The managers in the active arm will also receive the Prevail Managers programme which covers communication skills, problem formulation, and problem-solving skills. The questionnaire battery will then be given to both groups again 4 weeks post training, and 12 months post-training. Official records of absenteeism from Human Resources will also be gathered from both active and control groups at 12 months post-training.

**Discussion:**

The treatment trial aims to evaluate if Prevail reduces mental health related stigma (of a number of forms), increases help-seeking behaviours, and increases workplace productivity (via decreased absenteeism and presenteeism).

**Trial registration:**

ISRCTN12040087. Retrospectively registered 04/05/2020.

## Background

Common mental disorder (CMD, i.e. anxiety and depression) are indeed common, contributing around 16–17% of the burden of adult disease in the UK [1]. They are also major factors in sickness absence from work [2–5]. This has significant negative outcomes for both the employer and for the economy due to lost productivity.

The effects of CMD in the workplace may be more prevalent than most statistics suggest. First, individuals that are later diagnosed with a CMD are found to have increased visits to General Practitioners for other health reasons compared to controls [6] and have an increased number of days sick leave prior to a diagnosis of mental health problems [7]. Thus, sick days taken due to mental health problems are often recorded as due to other (physical) problems. Further, women with a psychiatric diagnosis also have a greater incidence of sick-leave due to non-psychiatric reasons, such as gastro-intestinal diseases [5, 8]. While this may reflect some co-morbidity (or a side effect of treatment) it also might suggest that the reasons given for sick leave may not always be accurate and that non-mental health reasons may be given as the reason for illness when the reason is due to poor mental health.

There have been several studies of treatment and therapies designed to enable people with CMD to return to work. Standard CMD treatments, such as cognitive behavioural therapies and psychotropic medication have significant effects on symptom reduction, but do not have an impact on return to work and only modest effects on amount of sick leave [9]. Perhaps more effective results might be obtained if there were more workplace-based interventions that involved co-operative sickness management plans that involved both the person and their employer working together for the benefit of both.

Workplace interventions specifically target the problem as it affects the person’s ability to function in the workplace and involve the active involvement of the employee. However, such a process is likely to be challenging as the employee and employer may have different perspectives and aims [10]. Nevertheless, there is some, although mixed, evidence that work-based interventions can reduce sick leave due to CMD [11, 12].

### Prevail

Prevail is a multi-faceted programme aimed at reducing sickness absence and presenteeism due to CMDs. It involves two psychological interventions, both provided via group based intervention programmes. The first (Prevail-Staff) is for all employees within the organization and its aims are to improve knowledge about mental health, including knowledge of best-practice in low intensity psychological inventions and the theoretical premises underpinning such interventions. It also aims to reduce stigma related to mental health issues, and in particular self-stigma [13], and thus promote help-seeking behaviours both within and outside of the workplace. It covers: i) the basics of mental health literacy; ii) the normalization of CMD; iii) attempts to reduce stigma associated with CMD, with an emphasis on self-stigma; and iv) a plan of managing CMD within the workplace to reduce distress and work-place functional impairment. This includes situations when simple adjustments in work-based practice may greatly assist, when low intensity psychological interventions are appropriate, and when professional psychiatric or medical help may be required.

The second intervention (Prevail-Manager) is aimed at the managerial level within the workplace and is designed to teach managers a formulation-based approach to evaluation and intervention. Formulation refers to a process of providing an explanation for the presenting problem and differs from a “diagnosis” which is more categorical and refers to the actual CMD rather than the causes, or trigger-factors, of the CMD. The focus here is on understanding, active problem-solving, and co-production (where both the employer and the employee share the responsibility to plan and deliver the intervention within the work-place and both make a contribution and commitment to this plan [14]), with the aim of preventing sick leave and enhancing productivity.

### Aims and hypotheses

This Protocol presents the design of a cluster randomised control trial to examine the effects of Prevail. We will include three levels of outcome: (i) mental health literacy, with emphasis on levels of mental health stigma and self-stigma; (ii) behavioural data (sick leave and presenteeism); and (iii) measures of mental health and quality of life.

We hypothesise that the employees who have undergone the Prevail intervention programme (which encompasses both the Prevail-Staff intervention and the Prevail-Manager intervention programme), compared to the employment-as-usual (EAU) group of employees, will have: (i) reduced levels of mental health stigma and increased willingness to seek help for CMD; (ii) fewer sick days in the 12 months following the Prevail intervention programmes (Prevail-Staff and Prevail-Manager); and (iii) lower levels of presenteeism (as estimated via self-report). Mental health and quality of life measures will also be taken in order to be able to take a baseline measure of health economics for later translation to a cost-benefit analysis and health economics evaluation of the Prevail intervention relative to productivity savings.

## Methods/design

A CONSORT statement was used to describe the study [15]. The study design is a two-armed cluster randomised control trial of Prevail to decrease mental health stigma (with a specific focus upon self-stigma) and increase help-seeking behaviour. This, in turn, should decrease absenteeism and presenteeism (see Fig. 1). The setting is the Driver and Vehicle Licencing Agency (DVLA). The DVLA is the executive agency part of the Department for Transport. DVLA maintain the registration and licensing of drivers and vehicles in Great Britain. It employs around 6000 people mainly at its headquarters in Swansea, Wales, UK.

**Fig. 1 Fig1:**
[figure not shown]
Consort Representation of Study

A clustered randomised control trial (RCT) design was deemed necessary as the Prevail programme addresses the two-way communication of mental health information and planning of active problem-solving and mental health interventions (and/or help seeking) between a manager and the employees within their team. Hence, both the manager and all members of their team had to be in the same arm of the intervention and the only way to achieve this is via a clustered RCT design. Hence, randomisation will take place at the level of the managers and will involve clusters of approximately 12 people (although this varies from division to division within the DVLA). However, the main outcomes (e.g. attitudes to mental health, absences from work) will be at the level of the individual employees of the DVLA and not at this cluster level.

### Recruitment and consent

Eighty managers across four divisions of the DVLA will be chosen by the DVLA to take part in the study on the basis of workload considerations. All managers will be given information about the aims and objectives of the study and will be asked by the DVLA to take part. However, participants will be blind as to whether they will be in the Prevail or Employment as Usual (EAU) group. These 80 managers will be managing approximately 960 employees.

Prior to the commencement of the Prevail intervention programme, managers and employees will be invited to a pre-intervention information session to explain the aims of the Prevail programme and be told that they have been selected as possible candidates for this psychological intervention. At this pre-session all participants (employees and managers) will be invited to complete the baseline evaluation measures. Completion of the baseline measures is voluntary and written informed consent will be taken at this time for those that wish to participate in the study and complete the evaluation measures. All participants and researchers are blind at this stage to as whether they are to be allocated to the Prevail (Active) group of Employment as Usual (Control) group. Any employees and managers who do not wish to participate in the research project will be free to leave the pre-intervention session without the need to justify their decision.

The 80 managers will then be allocated to the Active or Control arms of the study. Allocation will be random, but stratified by division and by the gender of the manager to ensure equal numbers within Active and Control groups across these variables. For managers and their teams in the Active arm of the study, the DVLA has mandated the Prevail intervention programme as part of their work commitments, but the evaluation of outcomes of this via the cluster RCT was not mandated.

For the two follow-up data collection waves: post-Prevail (termed wave 2) and 12-month follow-up (termed wave 3), the DVLA will mandate that staff in both the Active and Control arms of the research design attend follow-up sessions. At these sessions, participants will be briefed as to the progress of the Prevail intervention trial and will be invited to complete the psychometric measures as evaluation of the intervention programme. Once again, completion of the measures is voluntary and written informed consent will be taken at this time for those that wish to participate in the evaluation. Those participants who do not so wish are free to leave prior to completion of the psychometric measures.

Data from Human Resources (HR) records for the staff and managers in the study will be processed by the DVLA Human Resources staff. This data will only be communicated to the researchers at a group level (e.g., average number of sick days in the Prevail group as compared to the Control group over the last 12 months), separated by gender and age, etc., in order to ensure that the sickness absence data is anonymous to the research team. If the group size for any specific data (e.g., average number of sick days in the Prevail group over the last 12 months for females aged 60+, etc.) falls below an N of 10 this data will not be communicated to the research team in order to protect the identities of the staff group.

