#### Registered sick leave

Sick leave will be assessed in two ways. Our primary measure of sick leave will be records kept by the Human Resources department of the DVLA. Days of sick leave in the 12 months pre and post the Prevail intervention programme for employees in the Active intervention and EAU Control groups will be coded into “mental health reasons”, “physical health reasons” or “other” by raters blind to the group assignment of the employees.

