#### Blinding

This study will involve a cluster-randomisation design. The employees will be randomised before they give informed consent as they will be allocated to the Control or Active intervention group depending on if their manager has been allocated to the Control or Active groups. Given the nature of the intervention it will be impossible for the managers or the employees to be blinded as to which group they are in, although the pre-evaluation assessments using psychometric tests were completed blind to group allocation (with both the researchers and the employees being blind to this). Data analysis (e.g., evaluation of number of days sick leave taken, scoring of psychometric measures) will be done by a member of the research team who will be blind as to the group allocation of the employee.

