### Data analysis

Statistical analyses adapted for cluster-randomised controlled trials will be used with random effect logistic regression (for binary data) and linear regression (for continuous data) (see [25]). Should potential confounders prove to be unevenly distributed, we will adjust for these in the regression model (e.g., gender).

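### HR sick leave, a primary outcome, is to reach the researchers only as group averages, and the promised cluster-adjusted regression cannot be run on those

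*Protocol article*

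**What the plan says.** All references are to the protocol article.

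- *Registered sick leave*, under the primary outcome measures: "Our primary measure of sick leave will be records kept by the Human Resources department of the DVLA". Days are taken for the 12 months before and the 12 months after the intervention.
- *Recruitment and consent*: HR staff process the records. On what the researchers receive: "This data will only be communicated to the researchers at a group level". The example is the "average number of sick days in the Prevail group as compared to the Control group over the last 12 months", and the figures are "separated by gender and age, etc., in order to ensure that the sickness absence data is anonymous to the research team". Any figure whose group "falls below an N of 10 this data will not be communicated to the research team".
- *Data analysis*, on the models: "Statistical analyses adapted for cluster-randomised controlled trials will be used with random effect logistic regression". The logistic form is meant for binary outcomes, and a linear model covers continuous ones. Unevenly distributed confounders are to be adjusted for in the model. HR data are not treated separately.
- *Methods/design*, below Fig. 1: "the main outcomes (e.g. attitudes to mental health, absences from work) will be at the level of the individual employees".
- *Blinding*: data analysis, with evaluation of sick-leave days as an example, "will be done by a member of the research team who will be blind as to the group allocation of the employee".
- *Randomisation*: 80 managers, stratified by division and manager gender.

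**The concern.** The unit of randomisation is the manager's team. A valid comparison of sick days between arms therefore needs the variation between teams, either from individual records carrying a team code or from team-level summaries. The described release names neither. It also names no standard deviation and no analysis carried out by HR.

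Hypothesis (ii) in *Aims and hypotheses*, fewer sick days over 12 months, rests chiefly on this outcome. If the data flow stays as written, the trial can report two averages for it but cannot attach a defensible measure of uncertainty. A later analysis plan cannot repair this, because it can choose a model but cannot recover data the researchers never receive.

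**Working it through.** **Step 1: the plan's own figures.** *Statistical power* gives alpha 0.05, power 80%, standardised effect 0.30, 12 per team and ICC 0.05. Two-sidedness is my assumption.

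- Unclustered: n = 2 × (1.96 + 0.842)² / 0.30² = 174.4, so 175 per arm, as stated.
- Design effect: 1 + (12 − 1) × 0.05 = 1.55, as stated.
- Clustered: 175 × 1.55 = 271.25 per arm and 542.5 in total, matching about 271 and 542.

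So the sample size already allows for clustering, and the analysis has to do the same.

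**Step 2: what the release can support.** Take 480 people and 40 teams per arm (960 / 2 and 80 / 2) and a total variance of 1. The variance of an arm mean is

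0.05/40 + 0.95/480 = 0.00125 + 0.00198 = 0.00323 (= 1.55/480).

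About 39% of it (0.00125 / 0.00323) is the between-team part.

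- One mean per arm is two numbers for two unknown means. No degrees of freedom remain for any variance, within or between teams.
- Splitting by gender and age gives more numbers but no replicates of the randomised unit. Each cell pools people from many teams, and cells in the same arm share the same team effects. Differences between cells reflect gender, age and individual noise. They do not identify the between-team component.
- Averages before and after give a difference in change as a point estimate. They lose each person's pairing of the two periods, and the listed breakdowns do not name division or manager gender, the stratification factors.

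The random manager effect, the confounder-adjusted model and a design-based standard error are therefore all out of the researchers' reach.

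**Step 3: size of the error in a naive fallback.** Suppose standard deviations were also released and the arms compared as if individuals had been randomised. The standard error would be too small by the factor 1/√DE, and the true type I error would be 2 × [1 − Φ(1.96/√DE)].

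| ICC | Design effect (12 per team) | Type I error |
|---|---|---|
| 0.01 | 1.11 | 6.3% |
| 0.02 | 1.22 | 7.6% |
| 0.05 (plan) | 1.55 | 11.5% |
| 0.10 | 2.10 | 17.6% |

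At ICC 0.05, 1/√1.55 = 0.803, so intervals would be about 20% too narrow.

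**Step 4: what a proper analysis would retain.** A t-test of 40 against 40 team means (78 df, effect 0.30, ICC 0.05) has:

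- with 12 per team: variance of a team mean 1.55/12 = 0.129, SE of the difference √(2 × 0.129/40) = 0.080, power about 96%;
- with 6.8 per team (542/80): design effect 1.29, variance 1.29/6.8 = 0.190, SE 0.097, power about 86%.

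Individual data need not leave the employer for the trial to have a sound test.

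**The case against.** The best defence is that the text is looser than it first appears. It speaks of a group level, gives the arm mean only as an example, and leaves the list of breakdowns open. A team is also a group, and an average team of 12 clears the threshold of 10. The restriction is on what is communicated, and HR processes the records, so HR could fit the model itself. This stands as far as it goes: a valid analysis is not impossible in principle. But the article describes neither route. Team-level release would also meet the small-group rule, because team size varies by division. None would be withheld if every team had 12, and about 24% would be if sizes were Poisson with mean 12 (my assumption).

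A reader might infer four stronger things that the documents do not support:

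- *That the trial cannot test absenteeism at all.* Self-reported sick leave is collected from individuals and can go into the planned models, although it is secondary and banded. The stigma scale, the other primary outcome, is untouched.
- *That small-group suppression distorts the main comparison.* It affects subgroup figures only. An overall arm mean over roughly 480 people would not be withheld.
- *That the plan has an 11.5% type I error.* The plan proposes cluster-adapted methods, and with averages alone even the naive test could not be computed. The ICC of 0.05 is a general planning value, not one given for sick days.
- *That the Methods/design and Blinding sections flatly contradict the release.* The first concerns the level at which outcomes lie rather than how they are analysed. The second may mean self-reported days. Both need clarifying, but the firm conflict is between *Recruitment and consent* and *Data analysis*.

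**Conclusion.** The point holds for the HR sick-leave outcome and for the release as the article describes it. Group averages by arm, gender and age do not allow the researchers to run the cluster-adjusted, confounder-adjusted regression, and no standard error, interval or p-value that reflects randomisation by manager can be derived from them. This is a conflict between two statements in the same article, and the word "only" in the quoted restriction is what prevents it being read as mere condensation.

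The 11.5% figure (6.3% to 17.6% for ICC 0.01 to 0.10) shows why clustering could not simply be ignored if standard deviations were supplied. It assumes a two-sided 5% test and equal teams of 12. Because one of the two primary outcomes is affected, the matter should be settled before HR prepares the data.

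**What to change.** Amend *Recruitment and consent* to say that DVLA HR runs the trial statistician's prespecified script on the individual records. The file would hold a team code, a masked arm code, division, manager gender, and days before and after the intervention. HR would release only the model output: effect, confidence interval and ICC. Then reconcile *Data analysis*, by stating that the HR outcome is modelled in this way, and *Blinding*, by stating which sick-leave data the blinded researcher evaluates.

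The cost is protocol wording, one tested script and some HR time. HR staff already handle these records and no person-level data leave the employer, so the confidentiality aim is kept.

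One row per team (masked arm, stratum, n, mean and SD) for an 80-team analysis is an alternative only if the employer first agrees how it fits with the rule on groups below 10. Exempting small teams would weaken a stated safeguard, so this route is not as cheap.

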### Randomisation

The randomisation will take place at the level of managers (*N* = 80). Managers will be stratified by division of the DVLA [Information Technology Services (ITS), the Contract Centre (CC), Casework and Enforcement Group (CAEG), and Input Services Group (ISG)] and by the gender of the manager. This is to ensure that these variables are equally distributed across the two arms of the study. A computer-generated random sampling procedure will be used to ensure unbiased allocation to each group: https://www.sealedenvelope.com/.

